#### Participant timeline

Possible participants are invited to access the study's website [79] and, after carefully reading the information package, they are instructed to create an online account. The participants are then asked to answer a few demographic questions (i.e., report on their age, education, status on the labor market, and marital/co-habitation status) and complete the PHQ-9 to determine their eligibility for further evaluation. If eligible, a screening procedure is implemented. A short telephone interview screens out those people whose interest in the study is motivated by issues other than their mood (e.g., curiosity, practical/life problems, need for a psychological assessment). Applicants who do not meet the inclusion criteria are informed via email. They are thanked for their interest, given a summary score and interpretation for their PHQ-9 score, and encouraged to discuss their problems with a professional, if necessary. Information on how to reach a clinical psychologist or psychotherapist is also provided.

Participants meeting inclusion criteria will be randomly assigned to one of the two conditions: immediate online intervention condition (mHealth intervention) or the delayed-intervention condition (see the flow diagram in Fig. 3). Subsequent assessments consist of all the above instruments. Figure 4 shows the schedule of enrollment, interventions, and assessments.

**Fig. 3 Fig3:**
[figure not shown]
CONSORT flow diagram [49] showing subject allocation to the study conditions

**Fig. 4 Fig4:**
[figure not shown]
Schedule of enrollment, interventions, and assessments. *t_1x_ and t_2x_ represent weekly separate assessments

The participants in the mHealth intervention are assessed at pre-intervention (time 1, baseline), at mid-intervention (time 2, 2 weeks after baseline), at post-intervention (time 3, 4 weeks after baseline), and at 3, 6, and 12 months post-intervention (times 4, 5, and 6). The participants in the delayed-intervention condition are assessed before the waiting period (time 1, baseline), at mid-waiting period (time 2, 2 weeks after baseline), and at post-waiting period (time 3, 4 weeks after baseline).

Participants assigned to the mHealth intervention will be given access to the online application along with explicit instructions regarding the use of all of its sections. Participants will be given 4 weeks to complete the intervention, during which time weekly messages will be sent out to them. Messages include regular assignments designed for a complete and thorough use of the application's courses and exercises, and encourage the review of materials whenever possible. However, participants are free to use the application at their own pace.

After each week, participants’ application use is evaluated (see the *Application Use Scale* described above). Similarly, after each week of using the application, the participants are required to complete the CESD-R for close monitoring of their depressive symptomatology and individualized feedback on their emotional state.

Participants in the delayed intervention group are placed on a wait list for 4 weeks.

### Sample size

The sample size was estimated considering the exploratory nature of the two trials, in terms of investigating the feasibility of the design and methodology employed, as well as app-related usability aspects. As such, we followed current research practice exploratory protocols. For example, in an audit of sample sizes for pilot and feasibility trials being undertaken in the UK, Billingham, Whitehead, and Julious [80] have found that the median pilot study sample size for two-arm trials was 30 participants per arm, for continuous endpoints. Taking this into consideration, as well as promising results (i.e., large within-group effect sizes) reported by previous studies testing mobile phone applications for depression [81], a total number of 50 participants per study (i.e., 50 participants without depressive symptomatology and 50 participants with mild depressive symptomatology) was anticipated.

### Recruitment

Possible participants are approached through presentations at various events and ads in the media. Additionally, clinicians from the private practice area are contacted for referrals. Those interested in using the application are asked to provide their contact details and are subsequently contacted via email, at which point the enrollment procedure is described.

### Assignment to study group

The participants are assigned to one of the two trials, depending on their depressive symptomatology level (i.e., PHQ-9 score). Using the software Randomizer.org, participants are then randomly distributed to one of the trials’ conditions. Randomization is performed by a research assistant using a simple (unrestricted) randomization sequence that assigns two unique numbers per participant; the number assigned is either 1 or 2, according to the number of experimental conditions. To conceal the allocation mechanism, the same research assistant will monitor the assessments and allow access to the application for the participants in the wait-list control group, after 1 month. The principal investigator and the statisticians running the data analysis will remain blinded to the study condition until the completion of the study.

### Data collection, management, and analyses

#### Data collection methods

The data are collected within the application, in the Evaluation section, and transferred to our servers using an encrypted, secure (https) industry-standard transfer protocol.

The following strategies will be implemented to promote participant retention and follow-up completion. First of all, participants are reminded every week of the specific assessment that needs to be completed, through the Messages section, and are rewarded with more ”Energy” after completing it. Participants are also told that the weekly completion of the mood questionnaires allows the app to create a personalized profile of their mood (through the profile section) and, thus, give individualized feedback on their emotional state. Furthermore, the messages that the participants receive every week comprise gradual steps in covering the app’s content and exercises — every message refers to a new content and/or new exercise to be covered during that week, explaining its purpose and possible use, and, at the same time, encouraging the participant to come back the next week. Lastly, for the follow-up assessments, participants will receive new messages reminding them that the free use of the app was possible because of a research grant, for which the collection of this data is essential.

#### Statistical methods

Improvement in the primary outcomes measures scores within and between the groups (for each study) will be examined using mixed-effects linear regression analysis with a random intercept and slope over time (three assessments: baseline, mid-intervention, post-intervention) and fixed effects for intervention assignment. The 3-, 6-, and 12-month follow-up data will be analyzed in a separate fixed-effects model. The main analysis will compare groups (experimental and wait-list) in terms of cognitive vulnerability factors for the first trial, or level of depressive symptoms for the second trial. When analysis of secondary/other outcomes is performed, the error probability will be adjusted according to the number of group comparisons performed.

An intent-to-treat analysis will also be performed to examine participants who dropped out prematurely.

App usage data and user activity will be examined in an exploratory manner by comparing the participants’ self-reported activity with their actual app usage as captured by our software. This wealth of data will allow the possibility of pinpointing any obstacles to user adherence to the protocol, and will shed light on the reasons for dropouts or irregular usage patterns.

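### The primary mixed model names only an assignment effect across baseline, week 2 and week 4, so the term that carries the app's effect is not fixed; taken literally it is diluted towards zero

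*Protocol article*

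**What the plan says.** The Statistical methods section gives the aim first: "Improvement in the primary outcomes measures scores within and between the groups (for each study) will be examined". The tool is a "mixed-effects linear regression analysis with a random intercept and slope over time", and the sentence ends with the occasions and the fixed part: "three assessments: baseline, mid-intervention, post-intervention) and fixed effects for intervention assignment". The next statement of the primary comparison is "The main analysis will compare groups (experimental and wait-list) in terms of cognitive vulnerability factors for the first trial", with depressive symptoms taking that place in the second trial. Neither sentence names a visit, a change score or an interaction.

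The text under Fig. 4 (Participant timeline) places the three visits for the app arm "at pre-intervention (time 1, baseline), at mid-intervention (time 2, 2 weeks after baseline), at post-intervention (time 3, 4 weeks after baseline". The wait-list arm has the same three visits. Time 1 therefore precedes any exposure to the app.

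Under Sample size the plan is "a total number of 50 participants per study". Under Assignment to study group, allocation is made "using a simple (unrestricted) randomization sequence".

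**The concern.** Baseline is one of the three responses, and the only fixed term named is assignment. Randomisation makes the expected arm difference at baseline zero. An assignment main effect is then a weighted average of a zero difference, a week-2 difference and the week-4 difference. It is not the effect of four weeks of app use, and it does not measure differential improvement, which is the aim the same section states. Any chance difference between arms at baseline also enters the coefficient directly.

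Each trial's primary conclusion rests on this coefficient, with about 25 people per arm. If it is diluted, a real effect can be reported as null. If the analyst instead chooses the term after seeing the data, the primary contrast was not fixed in advance.

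**Working it through.** **Plan's own figure.** There is none to reproduce. The Sample size section bases 50 per study on pilot-trial practice and on large within-group effects in earlier work; it gives no between-group effect, SD, alpha or power.

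**Inputs from the article.** Visits at 0, 2 and 4 weeks; random intercept and slope; 50 per study; simple randomisation.

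**Assumed inputs.** 25 per arm, complete data, two-sided 5% test; time t = 0, 1, 2 in two-week steps; intercept SD 0.7, residual SD 0.5, slope SD 0.1 to 0.5 per step, intercept–slope correlation −0.3 to 0.3. For power, the true week-4 effect is 0.8 units. The week-4 SD is √(0.49 + 0.25 + 4 × 0.04) = 0.95 at slope SD 0.2 and √(0.49 + 0.25 + 4 × 0.09) = 1.05 at slope SD 0.3 (zero correlation), so 0.8 units is about 0.84 or 0.76 SD.

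**Step 1. What an assignment main effect estimates.** With V the covariance matrix of the three visits, the expected coefficient is w′δ, where w = V⁻¹1 / (1′V⁻¹1) and δ holds the arm differences at weeks 0, 2 and 4.

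With equal weights (random intercept only), as a share of the week-4 effect:
- linear growth: (0 + ½ + 1)/3 = 0.50
- full by week 2: (0 + 1 + 1)/3 = 0.67
- week 4 only: (0 + 0 + 1)/3 = 0.33

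The planned random slope moves the weights, in most settings towards baseline:

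| Slope SD (correlation 0) | Weights, weeks 0 / 2 / 4 | Linear | Full by week 2 | Week 4 only |
|---|---|---|---|---|
| 0.1 | 0.37 / 0.33 / 0.30 | 0.46 | 0.63 | 0.30 |
| 0.2 | 0.45 / 0.33 / 0.21 | 0.38 | 0.55 | 0.21 |
| 0.3 | 0.54 / 0.33 / 0.12 | 0.29 | 0.46 | 0.12 |

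Over the whole assumed grid the share is 0.03 to 0.54 (linear), 0.19 to 0.71 (full by week 2) and −0.14 to 0.37 (week 4 only).

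**Step 2. Simulation check.** Random intercept and slope models were fitted to 100 simulated trials per setting, true week-4 effect −0.80:

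| Setting | Main effect: mean, power | Arm-by-time (slope difference × 2): mean, power |
|---|---|---|
| Linear, slope SD 0.2 | −0.32, 0.27 | −0.79, 0.92 |
| Full by week 2, slope SD 0.2 | −0.43, 0.45 | −0.79, 0.92 |
| Linear, slope SD 0.3 | −0.22, 0.17 | −0.81, 0.84 |

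**Step 3. Baseline imbalance.** With 25 per arm, the chance baseline difference has standard error √(2/25) = 0.28 SD.

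**Step 4. If arm-by-time was intended.** With three equally spaced visits, twice the slope difference is the difference in change from baseline to week 4:
- SE = √[(2/25)(4 × slope variance + 2 × 0.25)]
- slope SD 0.2: √(0.08 × 0.66) = 0.230; 0.8/0.230 = 3.48; power 94%
- slope SD 0.3: √(0.08 × 0.86) = 0.262; 0.8/0.262 = 3.05; power 86%

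With a common baseline mean, the residual variance is Var(week 4) − Cov(baseline, week 4)²/Var(baseline). At zero correlation the covariance is 0.49 and the baseline variance 0.74:
- slope SD 0.2: 0.90 − 0.49²/0.74 = 0.576; SE = √(0.08 × 0.576) = 0.215; power 96%
- slope SD 0.3: 1.10 − 0.49²/0.74 = 0.776; SE = √(0.08 × 0.776) = 0.249; power 89%

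The gain depends on the intercept–slope correlation. At slope SD 0.3 and correlation +0.3, the residual variance is 1.352 − 0.616²/0.74 = 0.839, SE 0.259, power 87%. At −0.3 it is 0.848 − 0.364²/0.74 = 0.669, SE 0.231, power 93%. The unadjusted SE stays at 0.262 in both.

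**The case against.** The strongest reply is that the sentence is abbreviated. It names no fixed time effect either, although a random slope without a mean slope would be unusual. The plural form of the assignment term could cover an effect on both intercept and slope, and an effect on slope is the arm-by-time term. The declared aim covers improvement between groups as well as within them, which points the same way. This is also a condensed journal article, and a full formula may sit in an analysis plan that is not shown.

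Much of this stands. A reader might infer that the plan has left out the arm-by-time term and so will report half the true effect. The article does not support that: it never says the interaction is excluded, and one half is exact only for linear growth with equal visit weights. Nor does it make within-group change the treatment test, since the group comparison is named explicitly.

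Two things remain. The article does not simply defer the model: it lists the occasions, the random terms and a fixed term, and the named term does not deliver the stated aim. And on the favourable reading, no baseline constraint or adjustment is described. That the trials are exploratory and sized for feasibility lowers the stakes, but they still have declared primary outcomes and a declared main comparison.

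**Conclusion.** The point holds in a conditional form. The section does not fix which coefficient, at which visit, is the treatment effect. Fitted as worded, with baseline as a response and assignment as the only fixed effect of interest, the estimate is diluted: about half the week-4 effect in the simplest case, and from near zero (slightly negative at the extreme, for an effect seen only at week 4) to about 0.7 across the assumed settings. None of these shares is a figure from the article.

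If arm-by-time was meant, the bias disappears and what is left is a modest loss of precision: power of about 86–94% against 89–96% at zero intercept–slope correlation, with almost no gain at +0.3 and a larger one at −0.3. These figures rest on 25 per arm, complete data, a week-4 effect of 0.8 units (about 0.8 SD) and the variance components listed above.

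**What to change.** In Statistical methods, state that the primary estimate for each primary measure is the app-minus-wait-list difference at week 4. Take it from a mixed model with time as a category (0, 2 and 4 weeks), one common baseline mean for both arms (or baseline score as a covariate), and separate arm effects at weeks 2 and 4. State that within-group change is reported as description only.

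This changes wording alone: no new data, visits or participants. The article keeps the principal investigator and statisticians blinded until the study is complete, so the change can be made and dated before anyone sees results by arm. Adding screening PHQ-9 as a covariate is optional and not part of this point.

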### Objectives

The aim of this exploratory study is to test a newly developed app for decreasing cognitive vulnerability in the general adult population, and, respectively, reducing minimal symptoms of depression. To this end, two samples of participants will be recruited: (1) participants free of depressive symptoms, and (2) participants presenting with mild depression symptoms. Within each sample, the participants will be randomized to an active group (i.e., a group receiving preventive intervention) and to a wait-list control, respectively. The clinical utility of the application will be assessed by comparing randomized group scores within each sample type with respect to (1) depressive symptom level, (2) negative and positive effects, (3) satisfaction with life, and (4) behavioral and cognitive vulnerability factors involved in the onset of depression.

This study will capitalize on one of the main advantages of smartphones, namely broad accessibility. Simply, through this app, we aim to target the majority of smartphone owners, in an attempt to (1) remit minimal depressive symptoms (to prevent their escalation), (2) decrease general cognitive vulnerability for depression and promote protective behaviors, even in the absence of any symptoms, and (3) reduce general negative effect and increase satisfaction with life. This initiative is congruent with recent recommendations in the literature [39], as well as with basic CBT principles and empirical evidence, which indicate that supporting individuals in coping with non-clinical psychological distress can prevent symptoms from reaching clinical significance [40, 41]. In addition, this app is designed to promote continuous engagement, by incorporating tailoring, customization, and gamification elements, aimed at nurturing intrinsic motivation to use the app. Previous data show that one of the main problems with computerized CBT-based interventions is premature dropout [42–44]. Therefore, though effective and largely accessible [45, 46], these interventions often do not reach their maximum potential because users prematurely give up using them.

Borrowing from CBT principles, with a therapeutic package inspired from rational emotive behavior therapy (REBT) [47, 48], a new application (app) has been developed and will be tested to examine its benefits in decreasing cognitive vulnerability and reducing mild depressive symptomatology as risk factors for depression.

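### Intention-to-treat is written as an additional analysis of dropouts, so neither trial's primary comparison is committed to all randomised participants

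*Protocol article*

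**What the plan says.** The Statistical methods section of the protocol article plans a mixed-effects linear regression over baseline, mid-intervention and post-intervention, with random intercept and slope and a fixed effect for assignment. It then identifies the primary comparison: "The main analysis will compare groups (experimental and wait-list) in terms of cognitive vulnerability factors for the first trial", and depressive symptoms for the second trial. Neither sentence says who is included. A separate paragraph follows: "An intent-to-treat analysis will also be performed to examine participants who dropped out prematurely".

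Three other places bear on this:

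- Objectives says that "one of the main problems with computerized CBT-based interventions is premature dropout" and adds that "these interventions often do not reach their maximum potential because users prematurely give up using them". No rate is given.
- Data collection methods says that the data are collected in the app's Evaluation section, with weekly reminders through its Messages section.
- Sample size sets "a total number of 50 participants per study", with no allowance for loss.

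**The concern.** Intention-to-treat compares everyone randomised, in the arm to which they were assigned. It is a rule about who enters the primary comparison, not a way of studying people who left. The protocol's sentence departs from this in two ways. The word *also* makes intention-to-treat an addition to the main analysis, which suggests that the main analysis is something else. The stated purpose, examining dropouts, is not what such an analysis does.

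This is more than a detail left to an analysis plan. The article speaks on the point, and an analysis plan that followed it literally could report a completer comparison as the main result and still claim that an intention-to-treat analysis had been done.

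What is at stake is the protection given by randomisation. During the first 4 weeks only the app arm has an intervention to abandon, and its data collection runs through that same app. If those who leave are the ones doing poorly, a completer comparison compares selected app users with a less selected wait-list.

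**Working it through.** **No planned figure is in dispute.** The protocol gives no power, effect size, SD or dropout rate, so there is nothing to reproduce. The check has two parts: what the text commits to, and how large the consequence could be.

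**Part 1: the text.**

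- The main-analysis sentence names the arms and the outcomes but no analysis set.
- The intention-to-treat sentence is additional and directed at dropouts.
- Nothing says that the main analysis includes all randomised participants, and nothing says that it is limited to completers.
- The planned model can use incomplete records, but the text does not say that it will.

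**Part 2: size, under assumptions that are not in the protocol.**

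- True effect zero; standardised scores (SD 1, higher is worse) at baseline, week 2 and week 4.
- Correlation 0.6 between any two visits.
- Loss before week 4 in the app arm only, with logit P(loss) = a + b × (week-2 score).
- Slope b = 0.5 or 1.0 per SD, with a chosen to give 20%, 35% or 50% loss.

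Loss depends only on the week-2 score, and the expected week-4 score given week 2 is 0.6 × the week-2 score. Hence

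completer bias = 0.6 × mean week-2 score among those who stay.

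Numerical integration gives:

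| Slope b | App-arm loss | Mean week-2 score of stayers | Completer bias (SD) |
|---|---|---|---|
| 0.5 | 20% | -0.096 | -0.058 |
| 0.5 | 35% | -0.166 | -0.100 |
| 0.5 | 50% | -0.236 | -0.142 |
| 1.0 | 20% | -0.173 | -0.104 |
| 1.0 | 35% | -0.292 | -0.175 |
| 1.0 | 50% | -0.413 | -0.248 |

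Negative values favour the app. A simulation of 1,000,000 records per scenario agrees: 0.056, 0.100 and 0.139 SD at slope 0.5, and 0.105, 0.175 and 0.248 SD at slope 1.0.

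**The same data with everyone kept.** Week 4 was regressed on baseline and week 2 among those observed, then predicted for the whole arm. The resulting bias was within 0.002 SD of zero in all six scenarios. This stands in for a likelihood analysis of all available records. The planned mixed model itself was not fitted, but equal correlations and flat means are a special case of it (random intercept, no slope variance), so it should behave the same way here.

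**Against precision.** With 50 per trial split equally, SE = sqrt(1/25 + 1/25) = 0.283 SD. The bias is therefore 0.058/0.283 = 0.20 to 0.248/0.283 = 0.88 of a standard error. Allowing for the smaller completer arm, the worst case is 25 v 12.5: SE = sqrt(1/25 + 1/12.5) = 0.346, ratio 0.248/0.346 = 0.72.

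**The case against.** The strongest reply is that the planned model already does what is asked. A mixed model with a fixed effect for assignment, fitted to all available records, keeps early leavers in their assigned arm, and the check above finds essentially no bias in that case. On this view the sentence is only clumsy, and analysis sets are commonly defined in an analysis plan, which is not shown here.

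Part of this stands. A reader might infer that the main analysis is a completer analysis. The protocol does not say so, and no completer, per-protocol or adherent set is named. What remains is that the protocol does not commit the model to all randomised participants, and that listing intention-to-treat separately points the other way.

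A reader might also infer that dropout will be one-sided, will remove poor responders and will bias the app effect upward, or that dropout dominates this field. The documents support none of this:

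- They call dropout one of the main problems and give no rate, arm difference or direction.
- Wait-list participants are also assessed at 2 and 4 weeks and can be lost.
- App users who feel better may leave too, which would reverse the sign.
- Stopping the app is not the same as missing an assessment. Participant timeline schedules both assessments for the whole app arm, Data collection methods describes weekly reminders, and Monitoring study implementation has participants telephoned when they miss the CESD-R, the instrument for the second trial's primary outcome.

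These measures reduce the risk but do not remove it. The telephone contact is described for safety monitoring and for the CESD-R alone, so it does not cover the first trial's cognitive measures.

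Finally, the trials are declared exploratory and the bias stays below one standard error in every scenario. That bears on urgency. It does not make the sentence right, because the abstract states the aim as contrasting efficacy with a wait-list.

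**Conclusion.** The point holds in a limited form. The protocol misstates the purpose of intention-to-treat and places it beside the main analysis, so the primary comparison in each trial is not tied to all randomised participants and may be run on completers.

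The consequence is conditional. If the main analysis were completer-only and app-arm loss depended on poor mid-course response, the inflation under no true effect would be roughly 0.06 to 0.25 SD, or about 0.2 to 0.9 of the 0.28 SD standard error at 25 per arm. This rests on assumed loss of 20-50% in the app arm only, a log-odds slope of 0.5-1 per SD and a correlation of 0.6. With all available data the bias is about zero, provided loss is missing at random. If loss depends on unobserved week-4 outcomes, naming the set correctly would not remove all bias.

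Changing the analysis set would also not fully restore precision lost through missing data. As an illustration, 25 v 18 observed gives a 95% half-width of about 0.62 SD, against 0.57 SD with 25 v 25.

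**What to change.** Replace the intention-to-treat sentence in Statistical methods with: 'The primary analysis in each trial includes all randomised participants in the arm assigned, using every available T1-T3 observation in the likelihood-based mixed model; any completer or adherent analysis is a sensitivity analysis.'

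In Participant timeline, make explicit that the T2 (2-week) and T3 (4-week) assessments already scheduled are still requested after a participant stops using the app.

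The cost is wording only. The planned model already accepts incomplete records, and no sample-size figure changes. The small downside is some extra reminders to people who have stopped using the app.
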